## Patient Public Involvement and importance to the NHS

We have discussed similar studies of milk feeding with parents on the neonatal unit who tell us that the risks and complication associated with feeding preterm infants are very important issues. In addition, the James Lind alliance (JLA) priority setting [www.jla.nihr.ac.uk/priority-setting-partnerships/preterm-birth/top-10-priorities/](http://www.jla.nihr.ac.uk/priority-setting-partnerships/preterm-birth/top-10-priorities/) identifies feeding and nutrition as very important.

This trial is of major relevance to the NHS and studies interventions and outcomes highlighted in a recent top research priority setting in preterm infants.[13] Many parents wish to breastfeed or provide expressed breastmilk, and some parents are concerned about using cow-milk based products. Breastfeeding is a major national priority and is an intervention that has potential to benefit marginalised and poorly resourced groups. Our study focuses on gut inflammation which may be a proxy marker for a higher risk of NEC. NEC is a devastating condition, and half of the infants requiring surgery die or have long-term serious disability. HMBF products could represent an important cost for the NHS, but the total costs of these products even when given to all infants on a large NICU will still be substantially less than the costs associated with a single episode of surgical NEC. We will invite a parent or parent representative to join the TSC. We will liaise with Tiny Lives charity and Bliss UK to consider the implications of our trial findings and disseminate the results.

## Experience of research team members

We are an experienced research team, having recruited more than 1000 preterm infants to trials and studies in the last 10 years, including qualitative exploration of sensitive issue in parents whose babies did not survive. We are recognised internationally for our work on feeding and nutrition, and associated complications such as necrotising enterocolitis. We have worked closely with parents on all our studies, and conducted qualitative studies with parents who are approached to join more than one neonatal research study[14].

Trial organisational structure and responsibilities

Trial sponsor

The institution employing the chief investigator (Newcastle Hospitals NHS Foundation Trust) will act as sponsor

Trial steering committee

A Trial Steering Committee (TSC) will be established to oversee the conduct of the study. It is anticipated that the TSC will comprise the lead investigators, an independent chair and a user representative. The TSC will meet twice during the course of the study, once shortly after the start of the study and then annually or as required throughout the course of the study.

Data monitoring and ethics committee

This is a mechanistic study in which trial outcomes will not be analysed until study end. In addition, the dietary regimens used are un-blinded. We therefore do not plan to have a Data Monitoring and Ethics Committee

Trial management

The trial will be reviewed by the trial management group (TMG) at the end of an internal pilot phase (n=5 per trial arm) and key data reviewed. The TMG will consist of the key investigators [name] along with trial managers, and research nurses, and will meet by teleconference months, with more frequent meetings if needed in the set up and initial period of recruitment.

Trial registration

The trial will be registered on the International Standard Randomised Clinical Trial Number registry.

Trial sites

Three large tertiary neonatal units with considerable experience of intervention trials in high risk neonates: Royal Victoria Infirmary Newcastle, James Cook University Hospital Middlesbrough, and University Hospital Southampton.

Investigator responsibilities

Investigators will be responsible for ensuring that institutional (site specific) approval has been obtained as well as Agreements signed off by their Institution prior to the start of the study. Investigators are required to ensure compliance to the Clinical Trial Protocol, Investigators File and any other study instructions as required by the Sponsor or its representatives. Investigators are required to ensure the accuracy of the trial data according to the instructions provided. Investigators are required to allow access to study documentation or source data on request for monitoring visits and audits performed by, the Sponsor or any regulatory authorities. The Investigator may appoint co-investigators to assist with conduct of the study locally. All co-investigators must be listed as members of the research team and appropriately trained. The Investigator has overall responsibility for ensuring the conduct of the study locally.

Publication policy and dissemination of results

The results from the trial will be submitted for publication irrespective of the outcome. The Trial Steering Committee will be responsible for approval of the manuscripts prior to submission for publication. At the end of the study, infants’ parents will be able to request a copy of the results of the study from the investigator at that site.

Authorship of presentations and reports related to the study will be in the name of the collaborative group.

There will be no funder or sponsor role in data analysis, presentation or publication. Newcastle Hospitals NHS Foundation Trust will act as sponsor and will require access to study resources and documents in order to provide oversight of governance issues relating to trial conduct. Anonymised, summary data will be provided in publications and may be additionally shared with the funder if not included in published outputs. Individual patient data will be held according to current NHS permissions to enable their use in any future meta-analysis.

# Appendix 1: data items and definitions

At randomisation

• Date and time of birth

• Sex

• Confirmation of eligibility (full eligibility check)

• Date of parental consent

• Name of person taking consent

• Gestational age (in weeks and days)

• Recruiting hospital

• Study allocation

Baseline evaluation

• Birth weight (kg)

• Birth length (cm)

• Head circumference (cm)

• Ethnicity (NHS Ethnicity)

• Mode of delivery

• Use of antenatal steroids

• Date and time first trial intervention administered

Daily evaluations

• Record nutritional intake (type of feed, fortification and type)

- If fortification paused, reason

• If infant is nil by mouth and reason

• Check for SAE

• Record of withdrawal information if relevant

Weekly evaluations

• Weight (kg)

• Length (cm)

• Head circumference (cm)

End of study evaluation

• Weight (kg)

• Length (cm)

• Head circumference (cm)

We will use standard definitions of disease and outcomes refined and validated in our previous studies to collect data including

- Standardized forms for: NEC/gut complications; sepsis

Appendix 4

Suggested mineral and vitamin supplementation for CMBF and HMBF arms

Please note: adjustment should be made based on serum monitoring as routinely undertaken for preterm infants

| Arm | CMBF | HMBF | Age/point at commencement |
| --- | --- | --- | --- |
| Supplement |  |  |  |
| Dalivit | 0.3ml | 0.6ml | From full feeds |
| Vitamin K drops | Not needed | 50mcg | From full feeds |
| Iron | As per unit guidance | As per unit guidance | From 2 weeks after last transfusion or 4 weeks whichever later |
| Folate |  | 40mcg (0.5 ml) | From full feeds |

Appendix 5 Nutritional content of fortifiers

| **Nutrients** | **Unit** | **Mature human milk** 100 mL** | **NeoKare MMF/g** | Mature human milk 100 mL + 4 g (4 sachets) NeoKare MMF |
| --- | --- | --- | --- | --- |
| Energy | KJ Kcal | 289 69 | 17.99 4.30 | 360.96 86.20 |
| **Macronutrients** |  |  |  |  |
| Fat | g | 4.1 | 0.18 | 4.82 |
| Saturated fatty acids | g | ns | 0.08 | 0.33 |
| Carbohydrate | g | 7.2 | 0.4 | 8.80 |
| of which sugar (Lactose) | g | 7.2 | 0.34 | 8.56 |
| Protein | g | 1.3 | 0.27 | 2.38 |
| Salt (=sodiumx2.5) | g | 0.04 | 0.004 | 0.06 |
| **Vitamins** |  |  |  |  |
| Vitamin A | µg | 58 | 1.96 | 65.84 |
| Vitamin D | µg | trace | 0.018 | 0.072 |
| Vitamin E | mg | 0.34 | 0.0204 | 0.422 |
| Vitamin K | µg | ns | 0.024 | 0.096 |
| Vitamin C | mg | 4 | <0.001 | 4 |
| Thiamine (Vitamin B1) | mg | 0.02 | <0.001 | 0.02 |
| Riboflavin (Vitamin B2) | mg | 0.03 | 0.002 | 0.038 |
| Niacin (Vitamin B3) | mg | 0.2 | 0.044 | 0.376 |
| Vitamin B6 | mg | 0.01 | <0.0005 | 0.01 |
| Folic acid | µg | 5 | <0.1 | 5 |
| Vitamin B12 | µg | trace | 0.004 | 0.014 |
| Biotin (Vitamin B7) | µg | 0.7 | <100 | 0.7 |
| Pantothenic acid (Vit B5) | mg | 0.25 | NA | 0.25 |
| **Minerals** |  |  |  |  |
| Sodium | mg | 15 | 1.685 | 21.74 |
| Potassium | mg | 58 | 7.81 | 89.24 |
| Chloride | mg | 42 | 4.91 | 61.65 |
| Calcium | mg | 34 | 19 | 110.0 |
| Phosphorus | mg | 15 | 11 | 59.00 |
| Magnesium | mg | 3 | 1.57261 | 9.29 |
| Iron | mg | 0.07 | 0.003 | 0.08 |
| Zinc | mg | 0.3 | 0.036 | 0.44 |
| Copper | mg | 0.04 | 0.0035 | 0.054 |
| Manganese | mg | trace | 0.00022 | 0.001 |
| Fluoride | mg | ns | NA | ns |
| Selenium | µg | 1 | 0.203 | 1.812 |
| Chromium | µg | ns | <0.5 | <2 |
| Molybdenum | µg | ns | <0.10 | <0.4 |
| Iodine | µg | 7 | 0.73 | 9.94 |

**
[figure not shown]
**

| **Please complete for infants with at least 5 days NBM, gut surgery or abdominal diagnosis resulting in death** | | | | | | |
| --- | --- | --- | --- | --- | --- | --- |
| **PUFFIN ID:** | | | | | | |
| Onset of the episode: day when abdominal concerns were raised and enteral feeds stopped (dd/mm/yy) | | | | | -- / -- / -- | |
| End of the episode: day when enteral feeds restarted (dd/mm/yy) or infant died if before feeds restarted | | | | | -- / -- / -- | |
| **What was the diagnosis? (please tick ONE box only)** | | | | | | |
| Suspected NEC not fulfilling criteria for stage II  (nil by mouth and antibiotics for minimum of  5 days)* | | |  | Focal intestinal perforation  (no NEC) | |  |
| Definite NEC: stage IIA or IIB* | | |  | Septic ileus | |  |
| Advanced NEC without perforation:  stage IIIA* | | |  | Dysmotility/meconium plug/milk plug | |  |
| Advanced NEC with perforation: stage IIIB* | | |  | Other (specify): | |  |
| **See overleaf for definitions of NEC** | | | | | | |
| **How was the diagnosis made? (please tick multiple boxes if appropriate)** | | | | | | |
| Clinically and radiologically | | |  | During surgery  Date: _ _ / _ _ / _ _ | |  |
| Histologically* | | |  | During post mortem  Date: _ _ / _ _ / _ _ | |  |
| ***If histology performed, the results:** | | | | | | |
| Confirm NEC |  | Do not confirm NEC |  | Confirm other diagnosis | |  |

Appendix 6 Reporting forms

**
[figure not shown]
**PUFFIN Gut Form V1 150621

**
[figure not shown]
**PUFFIN LOS Form V1 150621

| Baby is diagnosed with NEC if at least one of the following clinical AND at least one of the following radiological features is present: | |
| --- | --- |
| Clinical (please tick) | Radiological (please tick) |
| Bilious gastric aspirates/emesis □  Abdominal distension □ Blood in the stool □ | Pneumatosis intestinalis □Hepatobiliary gas□  Pneumoperitoneum □ |

| **Bell’s stage** | **Systemic** | **Gastro-intestinal** | **Radiographic** |
| --- | --- | --- | --- |
| Stage IIA  (Definite NEC, mildly ill) | Increased desaturations Bradycardia  Temperature instability  Lethargy | Increased pre-feed gastric aspirate  Definite abdominal distension  Absent bowel sounds  Possible abdominal tenderness  Possibly bloody stools | Pneumatosis intestinalis |
| Stage IIB  (Definite NEC, moderately ill) | As IIA with  platelets <100x 10^9/^L  and/or metabolic acidosis:  BE< - 8mmol/L | Abdominal distension with definite tenderness  Possible abdominal wall oedema/erythema | As IIA with portal vein gas  Possible ascites |
| Stage IIIA  (Advanced NEC, bowel intact) | As IIB with mixed acidosis: pH<7.2  DIC: neutropaenia <1x10^9/^L  Severe apnoea  Hypotension requiring inotropes | Generalised peritonitis with severe tenderness and abdominal wall induration | As IIA with definite ascites |
| Stage IIIB  (Advanced NEC, bowel perforated) | As IIIA | As IIIA | As IIIA with pneumo -peritoneum |

| **Please complete for infants with at least 5 days antibiotics (or intent) unless being given for clear gut related pathology requiring gut form completion** |
| --- |
| **PUFFIN ID:** |

| Onset of the episode defined as start of the intravenous antibiotic/antifungal treatment for minimum of five days (dd/mm/yy): | | _ _ /_ _ /_ _ |
| --- | --- | --- |
| Was this episode microbiologically confirmed (in blood or CSF only)? | | YES □ NO □ |
| Name of organism: | Date of sample (dd/mm/yy): | Site:  Blood □ CSF □ |
| What IV antibiotic/antifungal was used for treatment of this episode? |  | |
| Duration of treatment (in days): |  | |

| **Definitions of confirmed and suspected LOS** |
| --- |
| **Microbiologically confirmed LOS** |
| 1. Onset of episode **more than 72 hours** after birth AND 2. Positive microbiological culture (blood or CSF) sampled with aseptic technique more than 72 hours after birth showing: potentially pathogenic bacteria (including coagulase negative Staphylococci, excluding skin contaminants and mixed flora) or fungi AND 3. Treatment (or intention to treat) for minimum of five consecutive days with intravenous antibiotics/antifungals after the above investigations performed.   *(If the infant doesn’t complete five days of treatment (for reasons such as transfer or death), but there exists documented intention to treat the episode for five days, this still meets the condition mentioned above)*  ***See over for clinically suspected LOS definition*** |
| **Clinically suspected LOS** |
| If the blood/CSF culture shows no growth/mixed flora or growth of skin contaminants AND infant is treated with intravenous antibiotics/antifungals for 5 consecutive days AND shows at least 3 or more of the following signs:   - Increase in oxygen requirement or ventilatory support - Increased frequency of apnea and bradycardia - Hypotension requiring treatment (volume, inotropes) - Poor peripheral perfusion (capillary refill time > 3s, mottled skin) - Irritability, lethargy or hypotonia - Ileus or enteral feeds intolerance (with or without abdominal distention) - Reduced urine output to < 1ml/kg/hour - Temperature instability - Glucose instability - Metabolic acidosis (base excess > -8 mmol/L and/or lactate > 2 mmol/L - C – reactive protein level > 15 mg/L - White cell count < 4 or >20 x 10^9^ cells/L or platelet count < 100 x 10^9^ cells/L |

| **Please specify the clinical/laboratory features leading to the decision to treat this episode:** | |
| --- | --- |
| Increase in oxygen requirement or ventilatory support |  |
| Increased frequency of apnea and bradycardia |  |
| Hypotension requiring treatment (volume, inotropes) |  |
| Poor peripheral perfusion (capillary refill time > 3s, mottled skin) |  |
| Irritability, lethargy or hypotonia |  |
| Ileus or enteral feeds intolerance (with or without abdominal distention) |  |
| Reduced urine output to < 1ml/kg/hour |  |
| Temperature instability |  |
| Glucose instability |  |
| Metabolic acidosis (base excess > -8 mmol/L and/or lactate > 2 mmol/L |  |
| C – reactive protein level > 15 mg/L |  |
| White cell count < 4 or > 20 x 10^9^ cells/L or platelet count < 100 x 10^9^ cells/L |  |

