| Randomisation | Minimisation using gestation (<28 weeks yes/no) and hospital site. Twins and triplets will be allocated to same study arm. Secured, password protected web-based randomisation using minimisation algorithm ([www.sealedenvelope.com](http://www.sealedenvelope.com) or similar) |
| Primary outcomes | Stool inflammatory marker (calprotectin) |
| Secondary outcomes | Fecal cytokine levels  16s gut microbiota profile  sIgA in stool  Urinary inflammatory markers (iFABP and similar)  Feed tolerance and growth-related outcomes  Neonatal morbidities and clinical outcomes |
| Duration of trial intervention | 36 weeks postmenstrual age or when fortifier no longer required (whichever earlier) |
| Duration of study | Recruitment period: 12 months  Total trial duration: 15 months |
| End of Trial | Discharge from neonatal unit |
| Safety assessments | Routine assessments until discharge from Neonatal Unit  Safety tracking during hospitalisation |

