### Additional secondary outcomes – growth and neonatal outcomes

We will collect a range of relevant secondary outcomes:

1. Growth – weekly weight, length and head circumference, absolute changes (g/kg/day and mm/week) and change in standard deviation score based on UK reference data from study enrolment until 36wca and/or discharge
2. Episodes of NEC, sepsis - confirmed and clinically suspected according to existing nationally agreed case definitions
3. Chronic lung disease, Retinopathy of prematurity (ROP), Intraventricular haemorrhage, Cystic PVL etc.
4. Days of intensive, high and low dependency care; age at discharge, total length of stay
5. Age at starting fortifier; tolerance, days not received due to intolerance, duration of breastfeeding; type of feeding at discharge (direct breast feeding, tube feeding etc.) etc.
6. Blood/urine work, serum biochemistry and other inflammatory and immune markers (blood and urine): hsCRP, lymphocyte subsets, plasma amino acids (PAA), where samples and funding allow

|  | Enrolment (baseline) | Day 7 | Day 14 | Day 21 | 36w or discharge | Total per infant |
| --- | --- | --- | --- | --- | --- | --- |
| Growth | x | x | x | x | x | 5 |
| Calprotectin | x | x | x | x |  | 4 |
| Stool cytokines |  | x |  | x |  | 2 |
| Stool 16s RNA | x | x |  | x |  | 3 |
| Stool sIgA | x | x |  | x |  | 3 |
| Urine inflammatory/ oxidative measures | x | x | x | x | x | 5 |
| Feeding tolerance etc. | x | x | x | x | x | 5 |
| Targeted bloodwork (PAA etc) |  | x |  | x |  | 2 |
| Clinical outcomes / safety | x | x | x | x | x | 5 |

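### Appendix 6 defines metabolic acidosis with opposite base-excess inequalities on the late-onset sepsis form and in the NEC staging table, so suspected sepsis could be misclassified in both directions

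*Protocol*

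**What the plan says.** The protocol section on additional secondary outcomes lists "Episodes of NEC, sepsis - confirmed and clinically suspected according to existing nationally agreed case definitions". The working definitions are on the reporting forms in Appendix 6.

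On the LOS form, clinically suspected LOS has three conditions:

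- Culture: "If the blood/CSF culture shows no growth/mixed flora or growth of skin contaminants".
- Treatment: "infant is treated with intravenous antibiotics/antifungals for 5 consecutive days".
- Signs: the infant "shows at least 3 or more of the following signs", followed by a list of twelve.

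One of the twelve is "Metabolic acidosis (base excess > -8 mmol/L and/or lactate > 2 mmol/L". The tick-list that follows repeats the same wording, and the bracket is left open both times.

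The NEC staging table, also in Appendix 6, uses metabolic acidosis as a stage IIB feature and defines it as base excess below -8 mmol/L.

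**The concern.** The two forms use the same label, analyte, cut-off and unit with opposite inequalities, so they cannot both be right. The LOS line also conflicts with its own label, because a normal base excess satisfies a criterion headed metabolic acidosis. Nothing elsewhere in the protocol corrects it. The wording is printed twice, which makes an error in reading the PDF unlikely.

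At stake is the classification of clinically suspected sepsis. The adverse events section also lists sepsis among the outcomes recorded and reported, without separating suspected from confirmed. The trial is open label at three sites. A criterion that one reader applies literally and another silently corrects invites inconsistent classification by staff who know the allocation.

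**Working it through.** The plan states no figure on this point, so there is none to reproduce. The check is of the logic of the criterion.

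**Step 1. Apply both directions to the same values.** The LOS form as printed is met if base excess (BE) > -8 or lactate > 2. In the NEC direction, keeping the lactate limb, it is met if BE < -8 or lactate > 2.

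| BE (mmol/L) | Lactate (mmol/L) | LOS form as printed | NEC-table direction |
|---|---|---|---|
| 0 | 1 | met | not met |
| -4 | 1 | met | not met |
| -7.9 | 1 | met | not met |
| -8.1 | 1 | not met | met |
| -12 | 1 | not met | met |
| -10 | 3 | met | met |
| 0 | 3 | met | met |

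The direction matters only when lactate is 2 or less. In that range the two rules give opposite answers, except at exactly -8, where neither is met.

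**Step 2. Carry this into the three-sign rule.** With the sign met by default, 3 of 12 becomes 2 of the other 11. The infants wrongly added are those who satisfy the treatment and culture conditions, have a BE above -8 with lactate of 2 or less, and have exactly two other signs. The infants wrongly dropped satisfy the same two conditions, have a BE below -8 with lactate of 2 or less, and also have exactly two other signs.

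**Step 3. Ask whether the net effect can be sized.** Among treated infants without a pathogen on culture, let

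- A = probability of at least 2 of the other 11 signs, and B = probability of at least 3;
- q = share with the acidosis sign in the NEC direction;
- r = share who lose the sign as printed (BE at or below -8, lactate 2 or less).

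Treat the signs as independent. Then

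- as printed: (1 - r)A + rB
- NEC direction: qA + (1 - q)B
- difference: (1 - q - r)(A - B)

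The protocol gives none of these inputs, so the following values are assumptions. Take each other sign at probability 0.10 and q = 0.20:

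- A = 1 - 0.9^11 - 11 × 0.1 × 0.9^10 = 0.3026
- B = A - 55 × 0.01 × 0.9^9 = 0.0896
- NEC direction: 0.2 × 0.3026 + 0.8 × 0.0896 = 0.132
- as printed: 0.303 if r = 0; 0.8 × 0.3026 + 0.2 × 0.0896 = 0.260 if r = 0.20

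With sign probabilities of 0.05 to 0.30, q of 0.05 to 0.40, and r equal to 0 or q, the ratio of printed to NEC-direction classification runs from 1.05 to 5.2. That spread is too wide to serve as an estimate. The direction is also conditional: the difference is positive only when q + r < 1. In this grid q + r never exceeds 0.40 + 0.40 = 0.80, so the choice of range guarantees an over-count. At q = r = 0.60 the factor is 1 - 1.20 = -0.20, a net under-count.

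**The case against.** The strongest reply is that the error may have had little effect in use. The sign is headed metabolic acidosis, and the tick-list asks which features prompted treatment, so a clinician is unlikely to enter a normal gas there. Some staff will read the line as a deficit larger than 8. This stands as a limit on the consequence, because the documents do not show how forms were completed. It does not rescue the text: a case definition should not depend on readers reversing its inequality, and the definition itself is not limited to features that prompted treatment.

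The reply is also right that the sign cannot create a case alone. The LOS form is completed only for infants with at least five days of antibiotics given or intended, outside clear gut pathology. The culture condition and two further signs must also be met. Both arms use the same form, so the error does not by itself favour either arm.

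A reader might infer three stronger things, none of which the documents support:

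- *Suspected sepsis is over-counted.* This needs literal use of the form and assumed sign frequencies. The error also removes infants.
- *Nearly every infant with a blood gas already has one of three signs.* This overlooks the entry conditions for the form and definition.
- *An arm's rate shifts by 6 to 11 percentage points.* This is 1/18 = 5.6% and 2/18 = 11.1%. The protocol gives no basis for one or two reclassified infants. Eighteen per arm is the target for complete sampling; with up to 50 recruited, 25 per arm gives 1/25 = 4% and 2/25 = 8%. The listed outcome also counts episodes rather than infants.

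**Conclusion.** The contradiction is certain and needs no assumption: Appendix 6 prints the same threshold under the same label in opposite directions, and the LOS version is met by a normal base excess. Its consequence is that clinically suspected sepsis could be misclassified in both directions if the form is read literally. The size, and strictly the net direction, cannot be estimated from the documents.

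The reach is narrow. The point touches one sign of twelve, in one component of one secondary outcome. The definition of microbiologically confirmed LOS does not use the sign. The primary outcome is stool calprotectin, and the sample size rests on that. This is an internal contradiction in an outcome definition, of minor to moderate severity.

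**What to change.** 1. Reconcile both LOS-form lines, in the definition and the tick-list, with the direction in the NEC staging table, and close the bracket. Since the protocol says that it follows nationally agreed definitions, the investigators should confirm the wording against their source.
2. Reissue the LOS form to all three sites.
3. Reclassify every LOS form that is not microbiologically confirmed, using the recorded base excess and lactate, whether or not the acidosis box was ticked. Rechecking only ticked boxes would leave out infants with a base excess below -8 and lactate of 2 or less, whose box may be empty.
4. Report how many episodes changed class, by arm and in each direction.

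The text change is two characters plus a bracket. The recheck is small: the CONSORT diagram supplied with the protocol shows 31 infants randomised, and only those with an LOS form need review. The work depends on the gas values being retrievable from clinical records. No infant's care changes, because classification follows the treatment decision.
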